### Sample Size Estimation

The sample size will be estimated from Phase II where participants will be randomly allocated into four groups (10 each group). Then the calculation will be considering the minimal difference between the mean of an analysis of variance results obtained from both gait speed and the displacement of the center of pressure (COP) as the primary outcome. Thus, the sample size will be estimated with a unidirectional alpha of 0.05 and an 85% statistical power. The sample determined by the calculation will be increased by 20% to compensate for possible dropouts.

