### Sample and Recruitment

Preselected individuals will undergo a general assessment, with personal information, and anthropometric measurements which will be kept confidentiality under the responsibility of the researcher for the study.

The study will be conducted in three phases: (1) to determine differences in PC and gait between individuals with congenital and acquired blindness, and with/without a guide stick when wearing shoes and while barefoot compared to sighted people; (2) a pilot study to observe the effects of a cerebellar anodal tDCS on PC and gait during a proprioceptive exercises protocol; and (3) the exercise protocol with sample size calculation from phase 2. Figure 1 displays the flowchart of the proposed study process.

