### Randomization

A randomization in blocks will be applied, in which the participants will be randomly allocated to one of the four groups: (G1 = active tDCS + dynamic proprioceptive exercises; G2 = sham tDCS + dynamic proprioceptive exercises; G3 = active tDCS + static proprioceptive exercises; and G4 = sham tDCS + static proprioceptive exercises). Randomization will be done at the website www.random.org and conducting by a person blind to the objectives and protocol of this study.

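### Phase III is sized on a difference between means observed in a pilot of four groups of 10, so the stated 85% power holds only if the pilot estimate equals the truth

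*Protocol article*

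**What the plan says.** The Protocol article, Sample Size Estimation, names the pilot as the source of the Phase III size: "The sample size will be estimated from Phase II where participants will be randomly allocated into four groups (10 each group". It then describes the target difference: "the calculation will be considering the minimal difference between the mean of an analysis of variance results obtained". The outcomes that supply it follow in the same sentence: "obtained from both gait speed and the displacement of the center of pressure (COP) as the primary outcome". The error rates are "a unidirectional alpha of 0.05 and an 85% statistical power", and the result is raised by 20% for dropout.

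Sample and Recruitment confirms the link, describing Phase III as "the exercise protocol with sample size calculation from phase 2". Randomization sets out four groups that cross active or sham tDCS with dynamic or static exercise.

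The article gives no numerical target difference, no SD from outside the pilot, no allowance for uncertainty in the pilot estimate, and no lower or upper bound on N.

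**The concern.** A pilot of this size can give a usable estimate of an SD. It cannot give a usable estimate of a treatment effect. Required N varies with the inverse square of the difference, so sampling error in the difference is magnified in N. A pilot that overstates the effect by chance produces a Phase III that is too small. One that understates it produces a Phase III that is needlessly large, or suggests that no trial is feasible.

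The nominal 85% describes power against whatever difference the pilot shows. It is not power against the true effect, nor against an effect that someone has judged worth detecting. At stake is whether Phase III can answer the question it is run for.

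**Working it through.** There is no stated Phase III N to reproduce, because the article gives no target difference or SD. What can be checked is how the rule behaves.

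**Inputs from the document:** four groups of 10; one-sided alpha 0.05; power 85%.

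**Assumptions:** true tDCS effect of 0.5 SD (0.8 SD as a second case), no exercise effect, normal outcomes, SD pooled over four groups (4 × 9 = 36 df).

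**Step 1. Precision of the pilot.** The standard error of a pairwise difference is √(2/10) = 0.447 SD. The 95% half-width is 2.028 × 0.447 = 0.91 SD.

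**Step 2. N if the true effect were known.** n per arm = 2(1.645 + 1.036)²/d² = 14.38/d². For d = 0.5 this is 57.5, so 58. For d = 0.8 it is 22.5, so 23.

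**Step 3. Chance of a wrong-sign pilot.** For G1-G2 at d = 0.5: Φ(−0.5/0.447) = Φ(−1.118) = 13%. For the pooled active-sham contrast (20 v 20) the standard error is √(2/20) = 0.316, giving Φ(−0.5/0.316) = Φ(−1.58) = 6%. Such pilots yield no usable difference for a one-sided calculation.

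**Step 4. True power after sizing on the pilot.** In simulated pilots, the observed standardised difference goes into the Step 2 formula. Power against the true effect δ is then Φ(δ√(n/2) − 1.645). For example, n = 11 with δ = 0.5 gives Φ(0.5 × 2.345 − 1.645) = Φ(−0.47), about 32%.

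Results at 0.5 SD, among pilots with the right sign:

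| Contrast used for sizing | Wrong sign | N per side, 10th–90th percentile | Mean true power | Below 50% | Below 85% |
|---|---|---|---|---|---|
| G1-G2 (10 v 10) | 13% | about 11 to 620 | 71% | 28% | 58% |
| Pooled active-sham (20 v 20) | 6% | about 17 to 475 | 76% | 18% | 53% |

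The N needed is 58 per side in both rows. In the first row a side is one group. In the second it is two groups together, so 29 per group.

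At 0.8 SD, mean true power is 78% (G1-G2) or 81% (pooled).

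**Step 5. The literal reading.** If the rule means the smallest of the six pairwise differences, the median N at 0.5 SD is about 1,900 per arm, or 4 × 1,900 = 7,600 in all. True power for that effect exceeds 99% in 97% of pilots. The error here runs the other way: the trial is infeasibly large.

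**The case against.** The strongest objection is to the wording. The sentence is garbled and need not mean the smallest difference among the four groups. It could mean one named contrast, the pooled tDCS effect, a pre-post change (Statistical Analysis defines effect size that way), or a minimal difference to be detected. This stands in part. A reader might infer that the plan commits to the smallest of six differences, or that Phase III is bound to be under-powered. The document supports neither. The literal reading over-powers, at a size nobody would plausibly run, which suggests that it is not what was meant. Under-powering follows only from other readings, and no Phase III N is stated.

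The one reading that would remove the problem is a minimal important difference fixed beforehand. The text does not support it: it refers to results obtained, names the pilot as their source, and gives no such value. A full protocol may hold a justified difference that this condensed article omits, but then the rule stated here contradicts it and still needs rewriting.

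A second objection is that G1-G2 is an unfavourable contrast, since the Introduction's hypothesis about tDCS can be addressed with 20 v 20. That is correct and makes the problem smaller, but more than half of right-sign pilots still lead to less than 85% power.

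Sizing from a pilot is also common practice. That is defensible for the SD, but not for the target effect.

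**Conclusion.** The point holds: the rule takes the target difference from means observed with 10 per group, and so does not deliver the stated 85%. At an assumed true effect of 0.5 SD, mean true power is 71% on a single contrast and 76% on the more favourable pooled one. The exact figures depend on the assumed effects of 0.5 and 0.8 SD and on which contrast is sized. The instability does not: each reading examined that uses observed pilot means either spreads N widely or inflates it beyond what is feasible. The direction of the error cannot be settled from the text. The rule should be changed before Phase III is sized.

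**What to change.** In Sample Size Estimation, delete the clause beginning "the calculation will be considering the minimal difference between the mean of an analysis of variance results obtained" and replace it with the following:

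- A stated and justified active-sham difference to be detected, one for gait speed and one for COP displacement, fixed before the Phase II data are seen.
- Use of the Phase II pilot only for the SD and the baseline-to-post correlation.
- The larger of the two resulting Ns, with a statement that 85% then applies to each outcome separately and not to both jointly. If the two were independent and each had exactly 85%, joint power would be 0.85 × 0.85 = 72%.

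Optionally, use the 80% upper confidence limit of the SD to allow for its uncertainty. With 36 df the factor is 1.12.

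The cost is a rewording, the work of justifying two differences, and a recalculation that is already planned after Phase II. N can no longer shrink after a lucky pilot. The optional SD limit raises N by about 25% (1.119² = 1.25), for example from 58 to about 73 per arm at 0.5 SD, before the dropout allowance. In a population that may be hard to recruit that is a real cost, so it should be a deliberate choice.

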### Randomization

A randomization in blocks will be applied, in which the participants will be randomly allocated to one of the four groups: (G1 = active tDCS + dynamic proprioceptive exercises; G2 = sham tDCS + dynamic proprioceptive exercises; G3 = active tDCS + static proprioceptive exercises; and G4 = sham tDCS + static proprioceptive exercises). Randomization will be done at the website www.random.org and conducting by a person blind to the objectives and protocol of this study.

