## Abstract

To maintain the balance, the postural system needs to integrate the three main sensorial systems: visual, vestibular, and somatosensory to keep postural control within the limits of stabilization. Damage of one of these systems, in this case, the vision, will have a great disturbance on the postural control influencing the behavior of the balance, resulting in falls. The aim of this study protocol for a randomized, controlled clinical trial is to analyze the effects of transcranial direct current stimulation (tDCS) combined with proprioceptive exercises on postural control in individuals with congenital and acquired blindness. In this randomized, controlled, double-blind, clinical trial, male, and female individuals with blindness between 18 and 55 years of age will participate in this study divided into three phases: 1—Determine differences in postural control and gait between individuals with congenital and acquired blindness with and without the use of a guide stick when wearing shoes and when barefoot; 2—A pilot study to analyze the effects a bilateral cerebellar anodal tDCS on postural on postural control and gait; and 3—A treatment protocol will be conducted in which the participants will be allocated to four groups: G1—active tDCS + dynamic proprioceptive exercises; G2—sham tDCS + dynamic proprioceptive exercises; G3—active tDCS + static proprioceptive exercises; and G4—sham tDCS + static proprioceptive exercises. Evaluations will involve a camera system for three-dimensional gait analysis, a force plate, and electromyography. Dynamic stability will be determined using the Timed Up and Go test and static stability will be analyzed with the aid of the force plate. The viability of this study will allow the determination of differences in postural control between individuals with congenital and acquired blindness, the analysis of the effect of tDCS on postural control, and the establishment of a rehabilitation protocol.

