Studies reported positive clinical effects with the use of tDCS combined with rehabilitation programs. In a meta-analysis (7) tDCS improved PC through the modulation of cortical excitability, which this technique could be a choice to enhance functionality and independence, and thus, reduce the rate of falls in individuals with a balance disorder, mainly on primary motor cortex (M1) stimulation. However, the effects of tDCS on the cerebellar cortex should be better investigated due to divergence in the study results. Are recognized that both early and late blind people have morphological changes in their whole brain, and the cerebellum is one of these structures. For example, Kosif et al. (8) showed a smaller volume of cerebellar area in congenital blindness subjects compared to sighted subjects. But systematic review studies showed positive effects of cerebellar tDCS to modulate cerebellocerebral networks (9, 10). But until the present, no study has investigated the effects of cerebellar tDCS on gait and PC in blind people.

As stated earlier for the visually impaired people, motor control is quite challenged even in simple tasks that require PC due to their blindness, and that tDCS induces cerebellar excitability changes (11), in which can modulate cerebellar-motor cortex excitability and thus, affect positively PC processing (12). The present study hypothesizes that tDCS can potentiate the effects of a proprioceptive exercises on both static and dynamic PC in blind subjects. The secondary objectives are (1) to determine possible differences in PC betweenindividuals with congenital and acquired blindness; (2) to evaluate the motor pattern of gait with and without the use of a guide stick when wearing shoes or while barefoot; and (3) to analyze whether proprioceptive exercises with or without tDCS can lead to different results with regard to PC.

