### Statistical Analysis

The data will be analyzed by Shapiro-wilk test to determine adherence to the Gaussian curve. If the parametric distribution is confirmed, the data will be expressed as mean and standard deviation, and for non-parametric variables, data will be expressed as the median and interquartile range. The effect size will be calculated based on the difference between means of the preintervention and post-intervention evaluations and will be expressed with their respective 95% confidence intervals.

An ANOVA or the Kruskal-Wallis test will be used for the analysis of the effects obtained in the phases one and two of the study. The Bonferroni correction for multiple comparisons will be employed as a *post-hoc* test. The analyses will be performed considering spatiotemporal gait variables, variables of COP parameters, and EMG signals as the dependent variables. The fixed independent variables in Phase I will be group (congenital and acquired blindness, and sighted), auxiliary resource (with and without guide stick), and shoes (with and without). In Phase II and III, the dependent variables will be the same as described in phase I, and for the fixed independent variables will be groups plus active and sham tDCS groups, evaluation time (preintervention, post-intervention, and follow-up) and group^*^evaluation time interaction. *P* < 0.05 will be considered indicative of statistical significance. The data will be analyzed using the Statistical Package for the Social Sciences (SPSS v.19.0) and Biostat (Analystsoft v. 2008.5.0.1).

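### Block randomisation is not stratified by congenital versus acquired blindness, so arms of 10 can differ on it by chance, mainly costing precision and cell size

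*Protocol article*

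**What the plan says.** The Randomization section of the protocol article states: "A randomization in blocks will be applied, in which the participants will be randomly allocated to one of the four groups". It gives no stratification factor. Group Allocation has each participant choose a sealed envelope in Phases II and III and mentions no separate sets by type of blindness.

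Sample Size Estimation fixes Phase II: "participants will be randomly allocated into four groups (10 each group". It leaves Phase III open: "The sample size will be estimated from Phase II".

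Onset type appears in several places:
- The Abstract states the aim as the effect of tDCS with exercises "on postural control in individuals with congenital and acquired blindness".
- The first secondary objective in the Introduction is "1) to determine possible differences in PC" between the two types.
- Statistical Analysis makes it an explicit fixed factor in Phase I. For Phases II and III the factors are "groups plus active and sham tDCS groups", then evaluation time and the group-by-time interaction.
- The Introduction cites a study that found a smaller cerebellar area in congenitally blind than in sighted people. The Intervention Procedure places the anode over the cerebellum.

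**The concern.** On the protocol's own reasoning, onset type may be related to postural control and possibly to the response to cerebellar stimulation. Blocking on arm alone does nothing to balance it. With 10 participants per arm, chance can leave one arm with clearly more congenitally blind participants than its comparator, or leave very few of one type in an arm.

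Phase II results set the size of Phase III, so a chance imbalance in Phase II can also distort the difference used for planning. The allocation scheme cannot be changed once participants are randomised.

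**Working it through.** **Inputs.** There are four arms of 10, so 4 × 10 = 40 participants (Sample Size Estimation). That size is set directly. No effect size, SD or Phase III total is given, so there is no calculated figure to reproduce. The congenital share is not stated either; I assume 30%, 40% and 50%, that is K = 12, 16 and 20 of 40.

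**Active v sham (20 v 20).** The number *a* of congenital participants on active stimulation is hypergeometric: P(a) = C(20,a) × C(20,K−a) / C(40,K). The gap is |2a − K|. For K = 20, a gap below 4 means a = 9, 10 or 11, with probabilities 0.205, 0.248 and 0.205. So P(gap ≥ 4) = 1 − 0.657 = 0.343.

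**G1 v G2 (10 v 10).** Let *s* be the congenital total in the two arms, hypergeometric (20 drawn from 40, K congenital). Given *s*, the count in G1 is hypergeometric (10 drawn from 20, *s* congenital). Sum over all cases with |2a − s| at or above the threshold.

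**Largest gap among four arms.** 200,000 simulated allocations.

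| Event, 10 per arm | 30% | 40% | 50% |
|---|---|---|---|
| G1 v G2, gap ≥ 3 of 10 | 23% | 26% | 27% |
| G1 v G2, gap ≥ 4 of 10 | 9% | 11% | 12% |
| Some pair of arms, gap ≥ 4 of 10 | 33% | 39% | 41% |
| Active v sham, gap ≥ 4 of 20 | 30% | 33% | 34% |
| Some arm has 0 or 1 congenital | 43% | 11% | 2% |

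**Do the blocks help?** No. With permuted blocks of 4 or 8 at a 50% share (20,000 runs each), some pair of arms still differs by 4 or more in 41% of runs.

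**Larger arms, 50% share.** The chance that some pair differs by at least 40 percentage points falls from 41% at 10 per arm to 19% at 15, 8% at 20 and 2% at 30. For active v sham, a gap of at least 20 points falls from 34% to 20%, 12% and 4%.

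**Cost in precision if onset type is in the model.** Adjustment inflates the variance of the treatment contrast by 1/(1 − r²), where r is the correlation between arm and onset type. For 7 v 3 congenital of 10, r = 0.4 and the factor is 1/(1 − 0.16) = 1.19. For 12 v 8 of 20, r = 0.2 and the factor is 1/(1 − 0.04) = 1.04.

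**Confounding if it is not in the model.**
- If onset type shifts the outcome by the same amount before and after treatment, the shift cancels from the pre-post change.
- If onset type alters the change itself by g SD, the unadjusted contrast moves by gap × g. Taking g = 0.5 to 1.0 (assumed), a 4-in-10 gap gives 0.4 × g = 0.2 to 0.4 SD, and a 4-in-20 gap gives 0.2 × g = 0.1 to 0.2 SD.

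**After stratifying.** With blocks of 4 in each stratum, any two arms differ by at most 1 participant of a given onset type. They do not differ at all when the stratum size is a multiple of 4, as it is in all three assumed cases.

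**The case against.** The other side has four good arguments.

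1. The article is a condensed account. It does not say that there is a single list, and a stratified scheme could be described in the full protocol or in Figure 1, which could not be consulted. That stands as a limit on certainty. But the article does describe both the method and its delivery, and neither description separates the onset types.

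2. If onset type is a model factor in Phases II and III, its main effect is adjusted for. This stands where the model is parametric and the factor is really there. The word for it is ambiguous, though: stimulation is listed separately, so the groups may be the onset types carried over from Phase I, or the exercise arms. The Kruskal-Wallis fallback named for Phase II has no place for a second factor. Adjustment also cannot fill thin cells.

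3. The planned effect size is a pre-to-post difference and the model tests group by time, so a constant level shift largely cancels. This stands. A reader might infer that any imbalance produces a spurious tDCS effect of 0.2 to 0.4 SD. The documents do not support that: the figure needs a 4-in-10 gap, no adjustment, and an onset effect on change that is assumed here.

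4. Small arms are documented only for the pilot. This stands, and the risk falls as arms grow.

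A reader might also infer that the aim requires comparing the tDCS effect between onset types. No such objective is stated. The aim names the population, and the first secondary objective concerns possible differences in postural control, which is the Phase I question. The cerebellar finding likewise compares congenitally blind with sighted people, not with people who lost sight later.

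**Conclusion.** The point holds as a moderate design weakness. The described allocation leaves a factor of declared interest to chance. At 10 per arm, with a congenital share of 30% to 50%, a sizeable imbalance in a named pair of arms is uncommon (9% to 12%). One somewhere among the four arms (33% to 41%), or a 4-in-20 gap between active and sham (30% to 34%), is not.

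The consequence is modest. At a 50% share, an adjusted contrast has about 19% more variance for a 7 v 3 split and about 4% more for 12 v 8. Cells average 5 congenital participants per arm at a 50% share and 3 at 30%. Confounding arises only if onset type alters the response to training or if an unadjusted or Kruskal-Wallis comparison is used.

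It would go too far to say that randomisation is invalid or that the tDCS estimate is biased by design, since chance imbalance does neither. The figures rest on the assumed congenital share and the Phase II size. They do not carry over to Phase III until its size is known.

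**What to change.** Before the first Phase II allocation, stratify the block randomisation in Phases II and III by onset type. Use one permuted-block list over G1 to G4 for congenital and one for acquired blindness, each with its own numbered envelopes opened in order; a free pick from a pile would undo the blocks.

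State explicitly in Statistical Analysis that onset type is a factor in the Phase II/III model, and say what the groups in that sentence are. If stratification is not adopted, say that allocation is unstratified and still name onset type as a covariate.

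The cost is one extra list and envelope set. Onset type must be defined and recorded before allocation; Sample and Recruitment gives only visual-acuity thresholds, so a written onset definition is needed. There may be one incomplete block per stratum, so with blocks of 4 total arm sizes may differ by up to two.

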### Group Allocation

An opaque and sealed envelopes will be used to conceal group information. After signing the informed consent, individuals will choose an envelope with the name of the group to which they will be assigned in phases II and III. This step will be managed by a third person who is not part of the study.

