## Materials and Methods

### Study Design

This study protocol is divided into three phases where phase 1 is a cross-sectional study to determine differences in postural control and gait between groups; phase 2 is a pilot study of phase three, a randomized, controlled, double-blind, clinical trial with blind individuals.

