### Blinding

The physical therapist that will conduct the evaluations will be blinded to the group assignment and to the objectives of the study.

To blind the sham group the stimulator will be turned on for only 30 s and then turned off. In this way, the subjects will have the initial sensation associated with electrostimulation but will not receive any stimulation in the remaining time.

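### Participants choose an envelope naming their group, so assignment need not follow the blocked list and the envelope could disclose active or sham stimulation

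*Protocol article*

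**What the plan says.** Four parts of the protocol article bear on this.

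- **Randomization** fixes the method: "A randomization in blocks will be applied, in which the participants will be randomly allocated to one of the four groups". The sequence comes from a website: "Randomization will be done at the website www.random.org and conducting by a person blind to the objectives and protocol of this study". No block size is given. The groups are defined by stimulation and exercise type, for example "G1 = active tDCS + dynamic proprioceptive exercises; G2 = sham tDCS + dynamic proprioceptive exercises".
- **Group Allocation** fixes how assignments reach participants. On concealment: "An opaque and sealed envelopes will be used to conceal group information". After consent, "individuals will choose an envelope with the name of the group to which they will be assigned in phases II and III". On who runs the step: "This step will be managed by a third person who is not part of the study". Nothing is said about numbering, about who opens the envelope, or about who reads its content.
- **Study Design** makes the masking claim: "phase 2 is a pilot study of phase three, a randomized, controlled, double-blind, clinical trial with blind individuals".
- **Blinding** covers the evaluating therapist, who is not told the assignment. For participants it relies on the brief sham: "the subjects will have the initial sensation associated with electrostimulation but will not receive any stimulation in the remaining time".

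**The concern.** Two things in the allocation step do not fit the rest of the plan.

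**The blocked list.** A blocked list constrains the allocation only if each new participant receives its next entry. If the participant selects the envelope, the selection decides the group. The two sections therefore describe different mechanisms. What is lost is the balance between groups during recruitment that blocking provides, and the means to check afterwards that each participant received the assignment generated for that position.

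**Masking.** The envelope carries the group's name, and the groups are defined by whether stimulation is active or sham. If that name reaches a participant or the staff who work with them, masking is lost at allocation, before any stimulation is given. Imitating the initial sensation cannot restore it. Gait speed is one of the two primary outcomes and the Timed Up and Go is done at a self-selected pace, so performance could respond to knowledge of the arm.

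The mechanism is stated for both randomized phases. It cannot be repaired once participants have been allocated.

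**Working it through.** The plan gives no figure for this point, so there is none to reproduce. The check compares two ways of issuing the Phase II assignments.

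**Inputs**

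- Four groups of 10, total 4 × 10 = 40 (Sample Size Estimation).
- Participant chooses the envelope (Group Allocation).
- Assumption: all 40 envelopes are on offer at the start and none is replaced. The article does not say how many are offered.
- Assumption for comparison: blocks of 4. The article gives no block size.

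**Blocks of four issued in order.** Each complete block holds one of each group. After 20 enrolments there are 20 / 4 = 5 complete blocks, hence 5 per group. The difference between the largest and smallest group is 0, so the chance of a difference of 4 or more is 0. The choice of block size is not critical here. With blocks of 8 (two per group), 20 enrolments are two full blocks plus 4 people, so the difference cannot exceed 2.

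**Draw from the whole pool.** The probability of group counts (a, b, c, d) with a + b + c + d = n is

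C(10,a) · C(10,b) · C(10,c) · C(10,d) / C(40,n).

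*Exact balance:*

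- n = 4: 10⁴ / C(40,4) = 10,000 / 91,390 = 10.9%
- n = 8: C(10,2)⁴ / C(40,8) = 45⁴ / 76,904,685 = 4,100,625 / 76,904,685 = 5.3%
- n = 20: C(10,5)⁴ / C(40,20) = 252⁴ / 137,846,528,820 = 4,032,758,016 / 137,846,528,820 = 2.9%

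*Difference between largest and smallest group at n = 20*, summing the formula over all possible counts:

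| Difference | Probability |
|---|---|
| 0 | 2.9% |
| 2 | 32.8% |
| 3 | 23.2% |
| 4 | 22.3% |
| 5 | 12.3% |
| 6 or more | 6.4% |

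A difference of 1 is impossible, because four counts that sum to 20 are either all 5 or spread over at least 2. A difference of 4 or more has probability 22.3 + 12.3 + 6.4 = 41.0%.

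**End of recruitment.** With a fixed pool all 40 envelopes are used, so the final split is 10/10/10/10 in either case.

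**Choice confined to the current block.** If participants chose only among the envelopes of the block being filled, block balance would be kept. The article does not say this.

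**Masking.** No arithmetic applies; the sections are set side by side. Randomization defines the groups by active or sham stimulation. Group Allocation puts the group's name on or in the envelope. Study Design claims double-blinding. Blinding offers only the sham sensation on the participant's side. No section says that the name is coded or withheld from the participant or the staff. The route to disclosure is therefore open, but no section describes disclosure taking place.

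**The case against.** The strongest reply is that the safeguards in the text are real. The envelopes are opaque and sealed, so the name is most naturally inside and unseen when the choice is made. Someone outside the study manages the step and may read the content without passing it on. Randomization also labels the groups G1 to G4, so the name might be no more than such a label. A sealed draw from a fixed pool is random and ends with equal groups. The article condenses a fuller protocol, where choice within a block might be specified.

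Most of this stands, and it limits the point in four ways.

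- A reader might infer that participants are unmasked. The article does not say that they open the envelope or hear its content. What can be said is that nothing stated prevents it. A label such as G1 would mask only if its meaning were kept from those who see it, and no such restriction is stated.
- A reader might infer selection bias or a non-random allocation. A choice among sealed opaque envelopes supports neither.
- A reader might try to attach a false-positive rate to an expectancy effect. The article gives no planned effect, which is to be derived from Phase II, and disclosure is not established, so no such rate follows from it.
- A reader might extend the point to imbalance in congenital versus acquired blindness, and ask for stratification. A properly issued unstratified blocked list has the same chance imbalance, so that is a separate design preference and does not measure this fault.

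Condensation does not remove the core of the point. The article does more than leave out the envelope procedure. It states a procedure, participant choice, that does not follow from its own randomization method.

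**Conclusion.** The point holds in a limited form. Randomization and Group Allocation must be reconciled, because as written the assignment need not follow the blocked list in either randomized phase. In Phase II the size is a chance of about 41% that the groups differ by 4 or more at the halfway mark, against 0 with ordered blocks. This rests on a draw from the whole pool of 40 and an assumed block size of four. If choice is confined to the current block, the loss of balance disappears.

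The harm is loss of balance during recruitment and of the link between list and assignment. Final group sizes and the randomness of the draw are not affected. Unmasking is a possibility that the wording leaves open, in a trial described as double-blind. It is not shown to occur, and no size can be put on it from the document. The point merits action before anyone is allocated because the remedy is nearly free and cannot be applied afterwards.

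**What to change.** Replace the participant's choice with these steps, and state them in Group Allocation:

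1. Prepare sequentially numbered, opaque, sealed envelopes from the blocked list, one per list position.
2. Have the independent third person already named open them strictly in number order, after consent, and record number and participant.
3. Put inside each envelope the exercise type and a coded stimulator setting, in place of the group name.
4. Keep the code key from participants and from the assessor, and say who holds it.

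The cost is re-preparing the envelopes and holding a code key. If the stimulator cannot be run from a coded setting, whoever sets it must know the code, and the article should say so. No participants or visits are added, and the sample size, alpha and power are unaffected.
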